### Study population and eligibility criteria

Potentially eligible ‌‌women in the two study sites are those aged 18 years or older diagnosed with early-onset preeclampsia at 24–34 weeks’ gestation [23]. Preeclampsia is defined as new-onset hypertension, characterised by systolic blood pressure of ≥140 mmHg or diastolic blood pressure of ≥90 mmHg, measured with an appropriately sized cuff at least 4–6 hours apart, and accompanied by proteinuria, defined as ≥300 mg in a 24-hour urine collection or ≥100 mg/L (equivalent to ≥2+ on dipstick urinalysis) in at least two random urine samples taken 4–6 hours apart after 20 weeks of gestation [2] and with no evidence of end-organ dysfunction. The exclusion criteria are women unwilling to provide informed consent, those with known allergy or hypersensitivity to NAC or any of its components, current use of medications or supplements that could interfere with the effects of NAC, such as other antioxidants, nitro-glycerine, activated charcoal, and chloroquine, receipt of a long course of mineral supplements containing NAC during the 6 months before enrolment, bleeding disorders, bronchial asthma, history of alcohol or drug abuse, active liver disease, significant chronic renal impairment, or major fetal anomalies, and women with preeclampsia with severe features or eclampsia at the time of randomisation.

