### Study outcomes

The primary outcome measure was time-to-disease progression (in days) among women with early-onset preeclampsia, defined as the interval from diagnosis to the first occurrence of a composite endpoint indicating clinical deterioration. Disease progression is defined as the development of any of the following: consistently elevated blood pressure of 160/110 mmHg or higher; severe proteinuria of 3+ or a urine protein/creatinine ratio of 0.3 or higher; platelet counts less than 100,000/µL; elevated liver enzymes (AST/ALT) or evidence of hepatic dysfunction; serum creatinine level greater than 1.1 mg/dL or doubling of baseline creatinine in the absence of other renal diseases; symptoms and signs of pulmonary oedema such as dyspnoea and crackles on lung auscultation; cerebral or visual disturbances such as headaches, visual disturbances, altered mental status, seizures (eclampsia), or other neurological symptoms; and evidence of placental dysfunction such as placental abruption, fetal growth restriction or oligohydramnios on ultrasound examination [2,5]. Participants who do not experience disease progression will be censored at delivery or at the end of follow-up. Secondary outcomes will include (1) safety and treatment tolerability, (2) maternal outcome (maternal mortality), and (3) composite neonatal outcomes, including low birth weight in term neonates (baby’s birth weight less than 2500g), IUGR, stillbirth, NICU admission, and perinatal and neonatal mortality. Women who develop preeclampsia with severe features will be managed as per the obstetric unit protocol and will be excluded from further participation in the study.

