### Randomization and allocation concealment

Participants will be randomly assigned using a 1:1 block random sequence of 4–6 blocks generated by the study statistician from Random Allocation software version 1.0 (May 2004) prepared in advance of the trial to receive either a daily oral tablet containing 600 mg of NAC or a placebo tablet to match the NAC tablets in size, shape, colour, and overall appearance to maintain blinding in addition to standard antenatal care from diagnosis (randomisation) until either 34 weeks’ gestation or delivery, whichever comes first [Fig 1]. The active drug (NAC) and placebo tablets will be packed in identical, coded, transparent dispensing sachets by the onsite pharmacy technician. The technician will then store the coded randomisation list in a sealed, opaque envelope, which will be kept in a locked file cabinet at the study site until the end of the study. The 600 mg oral daily dosage of NAC was selected after a careful review of the literature on the effectiveness of NAC in exerting antioxidant, anti-inflammatory, and antiproliferative effects while maintaining a favourable safety profile [16–21]. Furthermore, a low dose of 600 mg daily aligns with widely available commercial formulations that offer better gastrointestinal tolerability, which is important for sustained adherence in our study population and will also simplify procurement and ensure consistent dosing during the study. The placebo tablets will be composed of inert excipients, including microcrystalline cellulose, lactose, and magnesium stearate, and will contain no active pharmacological ingredient. Given the characteristic sulfur-like odour and taste of NAC, both NAC and placebo tablets will be administered with Coca-Cola Zero Sugar immediately prior to ingestion to mask any sensory differences and minimize the risk of unblinding. Participants, investigators, and outcome assessors will remain blinded to treatment allocation throughout the study period. To evaluate the effectiveness of blinding, a blinding assessment will be conducted at the end of the intervention period. Participants and study personnel will be asked to indicate their perceived treatment allocation (NAC, placebo, or unsure). The success of blinding will be assessed by comparing the distribution of guesses between groups against that expected by chance. All study participants, irrespective of treatment arm allocation, will receive standard-of-care management for early-onset preeclampsia in accordance with the institutional protocol and internationally accepted guidelines. The study intervention will only be administered as an adjunct to standard care, which will include corticosteroids for fetal lung maturation, antihypertensive treatment, magnesium sulphate for seizure prophylaxis (when indicated), close maternal and fetal monitoring, and delivery based on standard clinical indications.

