
**Fig 1 pone.0347695.g001:**
[figure not shown]
Trial flow chart.

**Follow-up evaluations:** Data collection will commence on the day the participant is randomized into the trial and will continue until the trial is terminated or the participant withdraws from the trial at any time for any reason. Study visits will be scheduled every two weeks until 32 weeks and weekly thereafter until delivery [Table 1]. Participants will be monitored using a daily symptom diary to record features of severity—headaches, visual disturbances (e.g., blurred vision, scotoma), dyspnoea, and right hypochondria or epigastric pain and any adverse event—gastrointestinal upset, dry mouth, nausea, vomiting, diarrhoea, rash, and fatigue and its severity using a daily symptom diary and present this for recording at their next clinic visit. At every follow-up visit, a newly filled dispensing sachet containing the experimental drugs with the same numeric code will be given to each woman, and the pills remaining in used sachets are then counted to assess adherence. Adherence will be defined as the use of at least 70% of the prescribed tablets for each participant. Allocations to treatment arms will be concealed from the study investigators, clinic staff, and trial statistician using sealed opaque envelopes that are sequentially numbered. The onsite pharmacy technicians will not be involved in the design, conduct, statistical analysis, and reporting of study findings. Additional information to be collected during the follow-up visits includes a history of allergies, level of treatment adherence, drug tolerability, bedside urinalysis for albumin, venous blood samples for biweekly measurements of haemoglobin, creatinine, liver enzymes (AST/ALT), and complete blood count. Serum biochemical assessments of glutathione and homocysteine levels will be performed at randomisation (baseline) and at weeks 28 and 32. Fetal growth scans and umbilical artery velocimetry (from 32 weeks) will also be done biweekly until delivery. At delivery, data on gestational age (in weeks), total duration of experimental drug intake (in days), intrauterine growth restriction (IUGR), neonatal birth weight (in grams), neonatal status at birth, 7th- and 28th-day (dead/alive), neonatal intensive care unit (NICU) admission, and length of NICU admission (in days) will be collected and recorded in the electronic CRF. Cord blood sampling at delivery for analysis of glutathione and homocysteine levels will also be collected to provide additional insight into maternal-fetal antioxidant transfer and potential downstream effects of NAC [Table 1].

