
**Table 1 pone.0347695.t001:** Time and events schedule.

Study Phase	Screening	Treatment/Follow-up Phase (Gestational Age)^a^												
Week		24–34 weeks	25 weeks	26 weeks	27 weeks	28 weeks	39 weeks	30 weeks	31 weeks	32 weeks	33 weeks	34 weeks	Postpartum	End-of-Study^b^
Inclusion and exclusion criteria	X													
Informed consent (ICF)^c^	X	X												
Sociodemographic and clinical information	X	X												
Randomization		X												
Oral NAC/Placebo dispensing			X	X	X	X	X	X	X	X	X	X		
Compliance assessment^d^			X	X	X	X	X	X	X	X	X	X		
Follow-up evaluation visits				X	X	X	X	X	X	X	X	X	X	
Primary endpoint (preeclampsia with severe features)						X	X	X	X	X	X	X		
Secondary endpoints						X	X	X	X	X	X	X	X	
Assessment of serum glutathione and homocysteine						X				X			X	
CBC, Renal and Liver Function tests		X		X		X		X		X		X		
Fetal growth scans and umbilical artery velocimetry										X		X		
Postpartum outcomes (NICU admission, neonatal mortality)						X	X	X	X	X	X	X	X	X
Study close-out														X
Adverse event review^e^	Continuous review													

a. There will be a minimum of 1 week between routine follow-up visits during pregnancy.

b. End of study is defined as 4 weeks postpartum or in case of early dropout.

c. Informed consent must be signed before any study-related procedures.

d. Drug compliance will be assessed via pill count and self-report thereafter.

e. Adverse events and concomitant medications will be monitored throughout the study, from the signing of the ICF onwards, until the participant’s last study-related activity or until the participant has been deemed lost to follow-up after demonstrating due diligence in follow-up efforts.

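### Table 1 stops scheduling primary-endpoint checks at 34 weeks although the analysis follows women to delivery, and entry and tablets share one undefined 34-week limit

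*Protocol article*

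**What the plan says.** **Entry.** Study population and eligibility criteria admits women "diagnosed with early-onset preeclampsia at 24–34 weeks" of gestation, with no days given for the upper limit.

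**Tablets.** Randomization and allocation concealment gives them "in addition to standard antenatal care from diagnosis (randomisation) until either 34 weeks" or delivery, whichever is earlier. The Abstract says the same.

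**Endpoint follow-up.** Study outcomes states: "Participants who do not experience disease progression will be censored at delivery or at the end of follow-up". Note b of Table 1 puts the end of study at 4 weeks postpartum or early dropout, so end of follow-up is not a 34-week cut-off. Data management and statistical considerations likewise censors deliveries without severe features and makes the primary analysis intention-to-treat.

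**Schedule in the text (Follow-up evaluations).** "Study visits will be scheduled every two weeks until 32 weeks and weekly thereafter until delivery". Blood counts, creatinine and liver enzymes are measured every two weeks, and "Fetal growth scans and umbilical artery velocimetry (from 32 weeks) will also be done biweekly until delivery". On supply: "At every follow-up visit, a newly filled dispensing sachet containing the experimental drugs with the same numeric code will be given to each woman".

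**Schedule in Table 1.** The last antenatal column is 34 weeks. The row "Primary endpoint (preeclampsia with severe features") is marked from 28 to 34 weeks only. The row "CBC, Renal and Liver Function tests" is marked at randomisation and at 26, 28, 30, 32 and 34 weeks. Growth scans are marked at 32 and 34 weeks. Dispensing ends in the 34-week column.

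**The concern.** The text and Table 1 give different instructions for detecting the primary endpoint. The composite includes low platelets, raised AST/ALT, raised creatinine, fetal growth restriction and oligohydramnios, all of which are found by a blood test or a scan. If staff work from Table 1, none of these is scheduled after 34 weeks, yet a woman who is undelivered and progression-free stays at risk in the Kaplan-Meier and Cox analyses. Events would be missed or dated late. If the two hospitals followed different sources, detection would also differ by site. With no drug effect both arms would lose events alike, so the cost is in events and accurate dates, not in false-positive risk.

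The second issue is exposure. Entry closes where tablets stop. Women near that limit get little or no study drug but contribute fully to the comparison, and all women undelivered after it are followed off treatment. Unless the effect carries over, this moves the hazard ratio towards 1 and makes a real effect harder to show.

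**Working it through.** **1. Text against Table 1**

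| Item | Text | Table 1 |
|---|---|---|
| Primary endpoint | Randomised women followed to delivery | 28 to 34 weeks |
| Blood tests | Every two weeks at follow-up visits, which run to delivery | Randomisation, then 26 to 34 weeks |
| Growth scans | To delivery | 32 and 34 weeks |
| Tablets | To 34 weeks or delivery | To the 34-week column |

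The column headed 39 weeks lies between 28 and 30 and is evidently 29, so it is not a later visit. The secondary outcomes refer to term neonates, so pregnancies beyond 34 weeks are foreseen. Before week 28 the gap is in the endpoint row only, because blood tests are marked at randomisation and at week 26.

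**2. Planned tablet days near the limit**

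If the limit is 34+0 (weeks+days) for both entry and stop, entry at 34+0 gives no planned days and entry at 33+0 gives at most 7. If it is 34+6 for both, the same holds one limit later. The documents do not say which applies.

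**3. Size of the dilution (illustration)**

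The plan gives no figure to reproduce here. From the plan: target hazard ratio 0.5, and 33.3% progression in controls (time horizon not stated). Assumed: entry spread evenly over the 10 weeks to the stop; control exits (progression or delivery) at r = 0.5 per week, one third of them progression; hazard ratio 0.5 on tablets and h afterwards.

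- Control exits after the stop: (1 − e^(−10r))/(10r) = (1 − e^(−5))/5 = 19.9%. For r = 0.25 and 1.0 it is 36.7% and 10.0%. With entry rising linearly towards 34 weeks, (2/100)(10/r − (1 − e^(−10r))/r²) gives 50.6%, 32.1% and 18.0% for r = 0.25, 0.5 and 1.0. An 11-week window (34+6 for both limits, even entry, r = 0.5) gives 18.1%.
- NAC arm on tablets: progression r/6, delivery 2r/3, total 5r/6 = 0.4167 per week. Share still in follow-up at the stop: (1 − e^(−4.167))/4.167 = 0.236.
- No effect after the stop (h = 1): NAC events are 0.2 × 0.764 = 0.153 on tablets and 0.236/3 = 0.079 off. Control events are 0.267 and 0.066. Off-tablet share of all events: 0.145/0.565 = 25.7%. Average hazard ratio ≈ exp(0.743 × ln 0.5) = 0.60.
- Partial effect (h = 0.7): NAC off-tablet events are 0.236 × 0.7/2.7 = 0.061, and the off-tablet share is 0.127/0.547 = 23.3%. Average ≈ exp(0.767 × ln 0.5 + 0.233 × ln 0.7) = 0.54.

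Cox simulations under the same assumptions (400,000 women per case) gave 0.537 and 0.596. Fast exit (r = 1.0, even entry) gave 0.52 to 0.55. Slow exit (r = 0.25, linear entry, all delivered within 3 weeks of the stop) gave 0.56 to 0.67. That slow case implies only about 25% control progression, below the planned 33.3%, so it is an outer case. The base case with h = 1 and the same 3-week limit gives 0.58.

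**4. Effect of separating the limits**

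Entry to 33+6 and stop at 34+6 leave every woman 1 to 11 weeks of planned tablets. Control exits after the stop become (e^(−0.5) − e^(−5.5))/5 = 12.0%. Repeating step 3 with (e^(−0.417) − e^(−4.583))/4.167 = 0.156 in place of 0.236:

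- h = 1: off-tablet share 0.092/0.554 = 16.6%, average 0.56.
- h = 0.7: off-tablet share 0.0805/0.543 = 14.8%, average 0.53.

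**The case against.** Following women after treatment ends is ordinary intention-to-treat practice, and stopping at 34 weeks may be deliberate in a trial of early-onset disease. Any dilution is conservative. All of this stands, so the stop itself is not called an error here.

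Table 1 is condensed and visibly rough. The text promises visits and scans to delivery, all women receive close monitoring as standard care, and operating procedures are to be written. This makes wholesale omission of tests less likely. It does not remove the conflict, because the text cites Table 1 for the visit schedule.

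The two harms also do not simply add. If Table 1 governed, fewer late events would be found and dilution would shrink.

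A reader might go further in three ways that the documents do not support:

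- **That the sachet sentence means dosing past 34 weeks.** The Abstract, the randomisation section and Table 1 agree on the stop, and the sachet sentence sets no treatment period. It needs a clarifying clause only.
- **That tablets must therefore continue to delivery.** That would change the intervention and lengthen exposure in pregnancy after ethics approval. It is a trade-off for the sponsor.
- **That the hazard ratio could drift to 0.61–0.76.** This range needs unlimited exit at 0.25 per week, so that e^(−0.25 × 8) = 13.5% of women undelivered at 34 weeks would still be pregnant beyond 42 weeks. It is not credible.

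**Conclusion.** The concern holds in two parts. The mismatch between Table 1 and the text is plain on the page and rests on no assumption: the endpoint, laboratory and scan rows end at 34 weeks, and the endpoint row starts at 28, while the analysis runs from entry to delivery. The shared, undefined 34-week limit is also plain, and it allows women to be randomised with few or no planned tablet days.

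The size of the dilution is not fixed by the documents, because entry mix, exit rate and carry-over are not given. A true 0.50 appearing as about 0.54 to 0.60 is a mid-range illustration, and full carry-over gives no loss. It covers all follow-up after the stop, not only that of the latest entrants. No power loss is quoted, because the sample size section states no event count. The point merits correction before recruitment but does not threaten the validity of the trial.

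**What to change.** 1. In Table 1, add an antenatal column from 34 weeks to delivery. Extend the primary-endpoint, laboratory and growth-scan rows through it, and start the primary-endpoint row at randomisation.
2. State the tablet stop in weeks and days, and set the entry limit below it, for example entry to 33+6 and stop at 34+6, so that every woman has at least 7 planned tablet days. If the stop is to be 34+0, closing entry at 32+6 does similar work: the off-tablet share of control exits becomes (e^(−0.5) − e^(−5))/4.5 = 13.3%, against 19.9%. Make the Abstract match.
3. In Follow-up evaluations, say that sachets are dispensed only up to that stop.

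**Cost.** A small amendment, notified to the ethics committee; recruitment had not begun at submission. Table 1 gains a few scheduled tests that the text already calls for. Closing entry a week earlier would lose about one entrant in ten if entry is even across the window. If the sponsor meant 34+0, a 34+6 stop adds up to 6 days of tablets. Separating the limits is a partial remedy, because women undelivered after the stop are still followed off treatment. Continuing tablets to delivery would remove that, but it is the sponsor's option and not a required correction.

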**Methods:**

This is the study protocol for a proof-of-concept, double-blind, randomized, controlled trial to be conducted between April 2026 to July 2028 at the maternity units of the two teaching hospitals in Lagos, Nigeria. At baseline, n = 153 sexually active women aged 18 years or older diagnosed with early-onset preeclampsia at 24–34 weeks’ gestation will be randomised to receive either daily oral tablet containing 600 mg of NAC or a placebo tablet that is matched for appearance and the dosing regimen in addition to standard antenatal care from diagnosis (randomisation) until either 34 weeks’ gestation or delivery, whichever comes first. The primary endpoint is the time-to-progression (in days) of early-onset preeclampsia to severe disease. The data analysis will be conducted on an intention-to-treat basis. Kaplan-Meier estimates with a Log-rank test will be used to calculate and compare the time-to-disease progression for the treatment groups, while Cox proportional hazard models with a backwards conditional method will be used to compare the primary endpoint between the treatment arms while adjusting for other covariates for precision using hazard ratios (HRs) and 95% confidence intervals (95%CIs). Subgroup analyses will also be performed to assess the differential effects of significant covariates on the impact of NAC on disease progression. Statistical significance will be reported as *P* < 0.05.

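### Masking of NAC's odour stops at the moment of dosing, so blinding is weakly supported for the participant who keeps the symptom diary and for whoever counts returned tablets

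*Protocol article*

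**What the plan says.** The section Randomization and allocation concealment promises "a placebo tablet to match the NAC tablets in size, shape, colour, and overall appearance to maintain blinding". The Methods part of the abstract describes a "placebo tablet that is matched for appearance and the dosing regimen". Neither list includes odour or taste. On composition the same section says: "The placebo tablets will be composed of inert excipients, including microcrystalline cellulose, lactose, and magnesium stearate".

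That section also acknowledges NAC's sulphurous odour and taste. Its answer, for active and placebo alike, is a drink with each dose: "placebo tablets will be administered with Coca-Cola Zero Sugar immediately prior to ingestion to mask any sensory differences". Tablets are "packed in identical, coded, transparent dispensing sachets by the onsite pharmacy technician". Participants, investigators and outcome assessors are declared blind for the whole study, and a treatment-guess questionnaire follows at the end of the intervention.

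Under Follow-up evaluations, a new sachet is issued at every visit and "the pills remaining in used sachets are then counted to assess adherence". The person who counts is not named. The same paragraph states: "The onsite pharmacy technicians will not be involved in the design, conduct, statistical analysis, and reporting of study findings". It also schedules biomarkers: "Serum biochemical assessments of glutathione and homocysteine levels will be performed at randomisation (baseline) and at weeks 28 and 32". Participants keep a daily diary of headache, visual disturbance, dyspnoea and upper abdominal pain.

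Study outcomes counts headache, visual and other neurological symptoms as disease progression, and lists dyspnoea among the signs of pulmonary oedema.

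**The concern.** The protocol names a sensory difference between the tablets and then masks it only while the tablet is being swallowed. A drink at that moment does nothing for a sachet that is opened every day, kept at home and brought back to clinic. This is more than detail left to a fuller document: the masking method is stated, and as stated it does not reach the hazard it was introduced for.

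What is at stake is the primary endpoint. Several of its components depend on what the woman reports and how a clinician interprets it. If either can guess the arm, symptoms may be reported or classified differently between arms. Study outcomes also ends participation once severe features are diagnosed, so later follow-up would not correct a doubtful symptom-based event. The end-of-intervention questionnaire can reveal a breach but cannot repair it.

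**Working it through.** No figure in the protocol settles this point. The check is a comparison of passages, followed by an illustration on assumed rates.

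**1. Where odour can be noticed, and what covers it**

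| Occasion | Person exposed | Masking described |
|---|---|---|
| Swallowing the daily tablet | Participant | Drink, both arms |
| Opening and storing the sachet at home | Participant | Visual match only |
| Return and pill count at each visit | Counter, not named | Visual match and coded sachet only |

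Only the first row has any sensory masking.

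**2. Link to the endpoint.** The participant is exposed on most occasions and also writes the diary. Headache, visual disturbance and dyspnoea appear both in the diary list (Follow-up evaluations) and in the composite (Study outcomes). This is the clearest route, and it needs no assumption about staff roles.

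**3. Who counts.** The technicians are said to take no part in conduct. Read literally, that leaves the count to clinic staff, from whom allocation is to be concealed. Yet the same technicians pack the sachets and store the coded list, which is itself part of conduct. Counting by clinic staff is therefore probable but not stated.

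**4. Biomarkers.** The Introduction calls NAC a glutathione precursor, so a rise from baseline could hint at the arm. Only sampling times are given, not who sees the results. The weeks are gestational (Table 1), so a woman enrolled after week 32 has no later scheduled antenatal sample. Cord blood is taken at delivery, when the primary endpoint has already occurred or been censored.

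**5. Illustration with no true effect**

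Inputs: 33.3% progression in both arms (Sample size calculation); evaluable women per arm 153 × 0.85 / 2 ≈ 65. The extra placebo events are assumed.

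Apparent HR = ln(1 − p_NAC) / ln(1 − p_placebo)

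(a) Extra events per 100 placebo women:
- 5 extra (about 3 of 65): ln(0.667) / ln(0.617) = 0.405 / 0.483 = 0.84
- 10 extra: ln(0.667) / ln(0.567) = 0.405 / 0.567 = 0.71

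(b) A fraction x of placebo women without progression wrongly called progressed, so p_placebo = 0.333 + 0.667x. The last column is a two-proportion normal approximation with 65 per arm, two-sided 5% test, in the direction favouring NAC.

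| x | p_placebo | Extra per 100 | Apparent HR | Chance of a false result favouring NAC |
|---|---|---|---|---|
| 0 | 0.333 | 0 | 1.00 | 2.5% |
| 3% | 0.353 | 2.0 | 0.93 | 4.3% |
| 5% | 0.366 | 3.3 | 0.89 | 5.9% |
| 10% | 0.400 | 6.7 | 0.79 | 12.0% |

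Sets (a) and (b) differ only in the denominator and are consistent with each other.

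**The case against.** The authors saw the risk. They named the odour, added a masking measure, declared all relevant parties blind and planned a blinding test. The excipient list is introduced with the word including, so an odour-matching ingredient is not ruled out. The documents do not say how strongly a stored or returned tablet smells. Most components of the composite are measured: blood pressure, proteinuria, platelets, liver enzymes, creatinine and ultrasound findings. The share of first events that are symptom-only is not given. All of this stands, and it limits the size of the point. It does not change the fact that the only sensory masking described ends at ingestion.

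A reader might infer more than the text allows:
- **That opened sachets reach blinded assessors.** The counter is not named, and nothing says that the counter also judges progression.
- **That glutathione results reach blinded staff.** No section says so. Restricting access to research biomarkers is a detail an article may leave to the full protocol or to the SOPs that Ethical considerations announces. Nor do the documents show that NAC at the trial dose shifts glutathione enough to identify one woman's arm.
- **That transparent sachets reveal the arm.** The tablets match visually, so transparency shows nothing, and opacity alone would not contain a smell.
- **That the HR shifts above estimate the bias.** They assume misclassification in one arm, in one direction, and only in women with no other qualifying event.

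**Conclusion.** The point holds as a gap in masking, not as demonstrated unblinding. The protocol admits a difference in odour and taste, matches on appearance, and masks only at dosing. The claim that blinding lasts throughout is therefore weakly supported for the participant and for whoever counts returned tablets. That clinic staff do the counting is a probable inference. The biomarker route is a precaution and not a defect in the text.

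The size of the risk cannot be derived from the documents. Under the assumed rates shown, an apparent HR between 0.93 and 0.71 could arise with no true effect, so a modest breach could matter in a trial of this size. The point is a cheap improvement, best made now: Trial status reports that recruitment had not begun at submission.

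**What to change.** 1. **Packs.** Use odour-barrier packaging, or equalise the odour of both arms' packs. Replacing transparent sachets with opaque ones is not enough. This addresses the participant's daily handling.
2. **Pill count.** Have used sachets returned closed to the pharmacy technician, or to another person who does not assess outcomes, who passes only the number to the clinic. Amend the Follow-up evaluations sentence on the technicians' role so that it allows packing and counting while still excluding outcome assessment, analysis and reporting.
3. **Biomarkers, as a precaution.** Confirm that maternal glutathione and homocysteine results from weeks 28 and 32 are withheld from investigators and outcome assessors until database lock, for example in a restricted REDCap form. Cord blood need not be covered to protect the primary endpoint.

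Cost: a packaging change, a few minutes of technician time per visit and an access setting. The site team would not see the on-treatment biomarker results during the trial; the article describes no use of them for care.
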